#### Follow-up

Six and 12 months after completion of the 12-week intervention phase, women will return to study centres for re-assessment of selected endpoints (mental health, health-related quality of life and physical activity questionnaires) to determine whether participants continued healthy lifestyle behaviours after the conclusion of the intervention.

### Outcome measurements

Outcome measures will be taken pre-intervention and post-intervention (Fig. 1). The primary outcome is the change in insulin sensitivity (measured by the steady state glucose infusion rate determined during the hyperinsulinemic-euglycemic clamp) between the three interventions. Secondary outcomes include reproductive health via hormone profiles (AMH and steroid profiles), mental health and health-related quality of life, body composition, physical activity behaviours and cardio-respiratory fitness.

## Data collection and analysis

### Anthropometric assessment

Following an overnight fast, participants will be weighed lightly clothed and without shoes (HW-PW200, associated scales services). Height will be taken without shoes using a calibrated stadiometer (Proscale Inductive Series I, Accurate Technology Inc.) and BMI calculated [weight (kilograms)/height squared (squared metres)]. Waist and hip circumference measurements will be taken [42] and the waist to hip ratio calculated. Fat mass, abdominal fat mass and fat free mass will be assessed using DXA (iDXA GE Lunar Prodigy scanner) and analysed by a qualified operator.

### Fitness parameters

Cardiorespiratory fitness via peak oxygen uptake (VO_2peak_) will be assessed using a symptom-limited graded exercise protocol on a cycle-ergometer [43]. The test will start after a 5-min period at rest. The protocol will consist of three 3-min stages at an intensity of 25 watts (W), 50 W and 75 W, respectively, and then an increase by 25 W every minute. The test will be terminated objectively when:Participant can no longer sustain a pedal rate greater than 60 rpmThere is no longer a change in VO_2_ with increasing work rateRespired expiratory rate reaches 1.1 or greaterAppearance of clinical signs or symptoms of metabolic or cardiorespiratory abnormalitiesPatient wishes to stop

Expired respiratory gases will be collected by the COSMED cardio pulmonary exercise test system breath-by-breath connected to automated gas analysers. The system will be calibrated before conducting each test using Hans Rudolph syringe and gases of known O_2_ and CO_2_ content (BOC gas). As a precautionary measure, 12-lead ECG will be monitored to minimise adverse events from undiagnosed cardiac arrhythmias during this testing.

### Physical activity and diet

Physical activity and exercise before baseline testing and before post-intervention testing will be monitored by a triaxial accelerometer (Actigraph™) for 7 continuous days. Average daily time spent in moderate to vigorous activity and METs will be calculated by the Freedson VM3 (2011) algorithms in Actlife software [44]. During the 12-week intervention habitual physical activity will be objectively assessed continuously using physical activity monitors (FitBit Flex™) and a smart phone application. Dietary habits will be assessed by a consecutive 3-day food diary before baseline and post-intervention testing. Food diaries will be analysed by FoodWorks® (Xyris) for the major food groups (grains, fruit, vegetables, protein and dairy), total energy and macronutrients.

### Self-reported measures

Participants will monitor their menstrual cycles using a menstrual diary, which will be used to assess menstrual cyclicity throughout the study. Self-reported physical activity questionnaires (IPAQ) [29] will be used to assess physical activity behaviour pre- and post-intervention. Mental health and health-related quality of life measures will be completed pre- and post-intervention to identify any changes in mental health and wellbeing after an exercise intervention and to determine the relationship with other outcome measures (DASS, SF-36 and PCOSQ) [30, 32, 45].

### Hyperinsulinemic-euglycemic clamp

Participants will undergo a hyperinsulinemic-euglycemic clamp to measure insulin sensitivity [3, 46, 47]. Human insulin (NovoNordisk ActRapid) will be infused at a constant rate (40 mU/min/m^2^) while a variable rate glucose solution is infused to meet the target of 5 mmol.L^− 1^ blood glucose in the last 30 min of the clamp. During the clamp, one hand will be warmed to improve blood flow for blood sampling. Blood samples will be taken every 5 min to monitor circulating blood glucose and an additional blood sample will be taken every 30 min during the clamp for insulin analysis. To reduce the risk of low potassium levels (hypokalaemia), participants will be given a single dose (600 mg) of slow-release potassium before the commencement of the insulin clamp.

### Pathology analysis

Glucose will be measured using an automated analyser (YSI 2300 STAT Plus). Insulin and N-terminal pro-peptide of type I and III collagen (collagen synthesis biomarkers) concentrations will be determined by radioimmunoassay according to manufacturer instructions (HI-14 K, EMD Millipore, UniQ PIIINP RIA #68570, UniQ PINP RIA #67034, Orion Diagnostica). Standard clinical pathology testing, including lipid profiles, haemoglobin A1c (HbA1c) and AMH, will be performed by a health pathology service. Serum steroid profiles, including testosterone, dihydrotestosterone, 3α and 3β androstanediols, estradiol, estrone, dehydroepiandrosterone (DHEA), androstenedione and progesterone, will be determined by liquid chromatography–mass spectrometry. Enzyme-linked immunosorbent assay (ELISA) will be used to measure transforming growth factor beta 1/3 (TGFβ1/3). To minimize variability, samples will be stored at (− 80 °C) and batch analysed by a single laboratory.

### Tissue biopsies

Vastus lateralis muscle and peri-umbilical fat biopsies will be carried out by a medical practitioner under local anaesthesia. After a local anaesthetic (1% xylocaine) is injected under the skin, a small incision is made to access the thigh muscle or peri-umbilical fat tissue and a small amount of each tissue is extracted from a consistent depth using a Bergstrom biopsy needle with suction [46]. Tissue samples will be used for the determination of DNA methylation profiles and protein levels of key tissue fibrosis molecules, insulin signalling proteins and TGFβ ligands before and after the 12-week intervention by western blotting.

### Western blotting

Protein levels of key tissue fibrosis molecules, insulin signalling proteins and TGFβ ligands will be measured by western blotting. Protein extraction and western blotting will be performed as previously described [27].

### Global methylation of peripheral blood mononuclear cell populations

Detailed methodology of peripheral blood mononuclear cell (PBMC) isolation and quantification has previously been described [48]. Briefly PBMCs will be isolated and collected by centrifugation by Ficoll gradient, before being stained for flow cytometry. A specific gating strategy to analyse T-helper cells, T cytotoxic cells, B cells and monocytes will be used to analyse the 5-methylcytosine quantity in each immune cell population.

### Statistical methods and determination of sample size

Primary analyses will be undertaken on an intention-to-treat basis, including all participants as randomised, regardless of treatment actually received. The HIIT group will be compared with the SSE and Con groups using a planned contrast of change from baseline to the week 12 endpoint on the basis of insulin sensitivity scores using a mixed-model repeated measures analysis. Stratification variables will be evaluated and retained in analyses where they are measured as significant or quasi-significant. Transformation of scores, including categorisation, may be undertaken to meet distributional assumptions and accommodate outliers. Comparisons of changes in insulin sensitivity scores from baseline to other time points will be undertaken as secondary analyses. Data will be analysed by SPSS and significance will be accepted when *p* < 0.05. Where required *p* values from the statistical analysis will be adjusted for multiple comparisons using the false discovery rate [49] and statistical significance will be accepted when false discovery rate q < 0.1.

Using the primary outcome of change in insulin sensitivity (as measured by the glucose infusion rate) of 27 mg/min/m^2^ (effect size (Cohens d) = 0.25) in response to training [4], we require a total of 42 participants or *n* = 14 per group to achieve a power of 85% (α = 0.05). With an approximate attrition rate of 30% based on previous research, we will recruit 60 participants [4, 12].

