### Randomisation and blinding

Following baseline testing, participants will be randomised to one of three 12-week interventions; HIIT, SSE or Con (details of the three treatment arms in Table 1). An independent biostatistician will randomise subjects by a simple randomisation procedure using computerised sequence generation with an allocation ratio of 1:1:1. Two tables based on BMI (< 35 kg.m^2^ or > 35 kg.m^2^) will be created. As exercise interventions cannot be blinded from participants and staff (accredited exercise physiologists) implementing the intervention, only staff undertaking sample analysis and endpoint data processing will be blinded to group allocation.

**Table 1 Tab1:** Details of the three treatment arms

Intervention	Details
Con	Standard care consisting of basic exercise advice (150 min/week) with no supervised or structured exercise. We do not anticipate the control group will engage in a significant amount of exercise compared to their baseline physical activity levels without the addition of a structured exercise program [11]
SSE group	Minimum physical activity recommendations (150 min per week) [40], in three supervised 50-min sessions/week of continuous moderate intensity exercise sessions of cycling at 50–60% HRR (~ 3.5 METs)
HIIT group	Minimum vigorous physical activity recommendations (~ 75 min per week) [40], in three supervised sessions/week of HIIT exercise (cycling/running). Based on existing literature, pilot data [43] and patient consultation, we will use a practical weekly training program encompassing two successful HIIT protocols [16, 17, 55]: two sessions/week of short constant load cycling of 12 × 1 min at > 85% HRR (> 9 METs; [1 min HIIT]) with 1 min active recovery; one session/week of cycling 6–8 × 4 min at > 85% HRR (> 9 METS; [4 min HIIT]) with 2 min active recovery

*Con* control- standard care, *SSE* supervised standard exercise, *HIIT* high-intensity intermittent training, *min* minutes, *MET* metabolic equivalent task, *HRR* heart rate reserve

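### The BMI stratum used at randomisation is kept in the analyses only if it tests significant in the trial's own data, so the primary model is not fixed in advance

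*Protocol article*

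**What the plan says.** Under Randomisation and blinding, the protocol article says "Two tables based on BMI (< 35 kg.m^2^ or > 35 kg.m^2^) will be created". BMI is the only stratification factor it describes. The same section has an independent biostatistician "randomise subjects by a simple randomisation procedure using computerised sequence generation with an allocation ratio of 1:1:1"; no blocks are mentioned.

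Under Statistical methods and determination of sample size, HIIT is compared with the other two arms "using a planned contrast of change from baseline to the week 12 endpoint on the basis of insulin sensitivity scores using a mixed-model repeated measures". The next sentence is the one at issue: "Stratification variables will be evaluated and retained in analyses where they are measured as significant or quasi-significant". It does not name BMI (the randomisation section supplies that link), does not exempt the primary analysis and gives no value for the looser of its two criteria. No other section fixes the covariates. Testing is at the level "significance will be accepted when *p* < 0.05", and the sample size statement is "we require a total of 42 participants or *n* = 14 per group to achieve a power of 85% (α = 0.05").

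**The concern.** A factor built into the allocation is normally carried into the analysis because of the design, not because of its p value. Here its place in the model is settled after the outcomes are seen. BMI was presumably chosen because it was thought relevant: the Background says obesity can worsen insulin resistance, and insulin sensitivity is the primary outcome. In a trial of about 42 completers, a significance screen says more about power than about relevance.

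Two things are at stake. The primary model is not pre-specified, so two defensible primary p values may exist. And if BMI does influence change, the contrast may be left unadjusted for chance imbalance. Separate tables filled by simple randomisation do not force the arms to be balanced within strata.

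**Working it through.** The plan gives no figure to reproduce. The reading rests on setting the two sections side by side; the arithmetic gauges the consequence.

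**Inputs from the protocol:** 42 evaluable women, 14 per arm, three arms, simple 1:1:1 randomisation, α = 0.05.

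**Assumptions (not in the document):** two-sided tests; half the women in each BMI stratum unless stated; stratum effect γ of 0, 0.5 or 1.0 within-stratum SD of change; looser cut-off read as p < 0.10 or p < 0.20.

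**1. Chance imbalance.** With 14 per arm and half the women in the upper stratum, the SD of the difference in upper-stratum share between two arms is √(2 × 0.5 × 0.5 / 14) = 0.19. At γ = 1.0 this adds 0.19² = 0.036 to the variance of the unadjusted contrast, which is otherwise 2/14 = 0.143. That is 25% more.

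**2. How often the stratum is kept.** For N = 42, upper-stratum share q and 38 residual df, the noncentrality is γ√(N·q·(1 − q)). At γ = 0.5 this is 0.5 × √(42 × 0.25) = 1.62 for q = 0.5, and 0.5 × √(42 × 0.21) = 1.49 for q = 0.3. Retention is then:
- p < 0.05: 30% to 35%
- p < 0.10: 43% to 48%
- p < 0.20: 58% to 63%

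At γ = 1.0 it is 90% to 94% for p < 0.10 and 95% to 97% for p < 0.20.

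**3. Type I error.** I simulated a linear model on change scores with one pairwise contrast and simple randomisation (20,000 runs per scenario, Monte Carlo SE about 0.0015). Ranges run over γ = 0, 0.5 and 1.0 and, for the mechanical rule, over the three cut-offs.

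| Use of the stratum | Type I error |
|---|---|
| Always included | 0.0495 to 0.0508 |
| One cut-off, applied mechanically | 0.052 to 0.055 |
| Free choice when the stratum p lies between 0.05 and 0.20 | 0.054 to 0.056 |
| Smaller of the two p values reported | 0.056 to 0.072 |

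**4. Power** for an assumed 1.0 SD contrast (8,000 runs, Monte Carlo SE about 0.005):

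| γ | Always included | Always omitted | Difference |
|---|---|---|---|
| 0 | 70.2% | 71.1% | −0.9 |
| 0.5 | 69.9% | 69.1% | +0.8 |
| 1.0 | 70.2% | 61.6% | +8.6 |

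The comparison is with always omitting the stratum. The rule applied mechanically gives 69.9% to 70.2% at γ = 1.0, so inclusion does not gain 9 points over the rule itself.

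**5. Which BMI term matters.** The clamp is scheduled only at baseline and after the intervention; the 6- and 12-month visits list questionnaires only. Write woman i's value at time t as group, time and group-by-time terms plus β·BMIᵢ. Her change is the week-12 value minus the baseline value, and β·BMIᵢ cancels. In one simulated complete dataset (42 women, three arms) the contrast was 0.3418 (SE 0.3197, p = 0.285) both with and without a BMI main effect. Adding BMI-by-time changed the result. With 30% of week-12 values missing, the main effect caused only small shifts.

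**The case against.** The strongest reply is that the rule may do nothing to the primary test. In a two-time-point model with group-by-time, keeping or dropping a BMI main effect leaves the p value unchanged with complete data. This stands. The criticism bites only if BMI-by-time is the term screened, or if change or the week-12 value is the outcome. The protocol does not say which, so the fix must cover both.

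It can also be said that the rule mostly discards BMI when discarding is cheap: at 0.5 SD, inclusion and omission differ by 0.8 points of power, and at 1.0 SD the factor is kept in 90% or more of trials at p < 0.10. That stands too, and it limits the size of the point.

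Finally, an article may leave a numerical cut-off and exact model terms to a full protocol or SAP. Agreed: the missing number is not the finding. The article does state a rule, however, and an SAP that followed it would still choose the model from the data, whatever the cut-off.

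A reader might go further in two ways that the document does not support:
- *Omitting the stratum gives standard errors that are too wide.* That needs allocation restricted within strata. With blocks and a 1.0 SD effect, always omitting the stratum gives a type I error of 0.031. The protocol specifies simple randomisation, under which the unadjusted analysis holds its level (0.050 to 0.052 in the same simulation).
- *A real BMI effect would be dropped in half or more of trials.* At 0.5 SD this is so for cut-offs of 0.05 and 0.10, but not for 0.20, where it is kept in 58% to 63%.

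**Conclusion.** The point holds as a defect of pre-specification with a modest numerical consequence. The protocol makes the presence of its own randomisation factor depend on the outcome data and does not exempt the primary analysis. The excess in type I error is about half a percentage point or less under mechanical use. It is about 2 points at worst, and that worst case requires reporting the smaller p value, which the protocol does not authorise. The power figures favour inclusion over omission only when BMI strongly affects change.

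All these sizes rest on the assumed stratum effects, the even split between strata and a change-score model. That the rule is data-dependent rests on the text alone. It should be corrected because the correction is nearly free, not because the trial's conclusions are in serious danger.

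**What to change.** Replace the retention sentence with:

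> The BMI stratum used at randomisation is included in the primary and secondary models regardless of its significance; where baseline is modelled as a repeated outcome, both BMI stratum and BMI stratum-by-time are included, and where change or week-12 value is the outcome, BMI stratum is included as a fixed factor.

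This changes one sentence and uses one or two degrees of freedom. On the assumptions above it costs about 1 point of power if BMI has no effect. It needs no new data and leaves the design and sample size as they are.

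### The plan allows the continuous primary outcome to be categorised; it should stay on one continuous scale, fixed before unblinding

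*Protocol article*

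**What the plan says.** Under Outcome measurements, the primary outcome is the change in insulin sensitivity, "measured by the steady state glucose infusion rate determined during the hyperinsulinemic-euglycemic clamp". This is a rate on a continuous scale.

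Under Statistical methods and determination of sample size, HIIT is compared with the other two arms "using a planned contrast of change from baseline to the week 12 endpoint on the basis of insulin sensitivity scores", by a mixed-model repeated measures analysis. Two sentences later comes the rule at issue: "Transformation of scores, including categorisation, may be undertaken to meet distributional assumptions and accommodate outliers". It names no transformation and makes no exception for the primary outcome.

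The sample size in the same section rests on a change of 27 mg/min/m², labelled "effect size (Cohens d) = 0.25", with 85% power at α = 0.05: "we require a total of 42 participants", or 14 per group. It continues: "With an approximate attrition rate of 30% based on previous research, we will recruit 60 participants".

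Under Randomisation and blinding, staff who analyse samples and process endpoint data are blinded to allocation. The section does not say who decides on a transformation, or when.

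**The concern.** A log transform keeps the outcome continuous and keeps a contrast of means. Categorisation does neither. It replaces a difference in mean change with a difference in the proportion of women beyond some cut-point, and the cut-point then becomes a choice of its own. It is also a costly answer to skewness or outliers, because it discards the ordering of values within each category. With about 14 analysed women per arm, there is little precision to give away.

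A second, smaller matter is timing. Whether assumptions hold and whether outliers exist can be judged only once outcome data are in hand. If the person choosing the scale could also see the arm comparison, the nominal 5% level would no longer be assured.

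**Working it through.** **Inputs from the Protocol article.** 14 analysed per group, 42 in total; 60 recruited; 30% attrition; 85% power; α = 0.05; allocation 1:1:1; outcome in mg/min/m².

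**Assumptions made here.** Two-sided test; a two-arm comparison of one arm with another; normal data for the efficiency and power figures; stated distributions for the type I error figures.

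**The plan's own figure.** The attrition step reproduces: 42 / 0.70 = 60. The 42 does not follow from the stated inputs. A between-group d of 0.25 at 14 per group gives 9–10% power. A 3-group by 2-time interaction with f = 0.25 and a correlation of 0.5 gives 80.3% at N = 42, and it reaches 84.5% only with an unstated correlation of about 0.55. That is a separate matter. Below, 85% at 14 per arm serves only as the reference from which loss is measured.

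**Step 1: information kept.** For k equal-sized groups cut from a normal outcome at quantiles q₁…q₍ₖ₋₁₎, efficiency is k·Σ(φ(qᵢ₋₁) − φ(qᵢ))², where φ is the standard normal density, taken as 0 at the two ends.

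| Groups | Kept | Lost |
|---|---|---|
| 2 (median split) | 2/π = 0.637 | 36% |
| 3 | 0.793 | 21% |
| 4 | 0.861 | 14% |
| 5 | 0.897 | 10% |

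For a median split, 14 × 0.637 = 8.9 per arm and 42 × 0.637 = 26.7 in total.

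**Step 2: power after a median split, by formula.** The standardised difference with 85% power at 14 per arm is d = (1.960 + 1.036) × √(2/14) = 1.13.

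- Efficiency formula: 1.13 × √(8.91/2) − 1.96 = 0.43, and Φ(0.43) gives 67%.
- Two-proportion formula: the proportions above the median are Φ(1.13/2) = 0.714 and 0.286, which gives 63%. Restoring 85% would take 23 per group.

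**Step 3: power after a median split, by simulation.** With the exact t distribution, 85% power needs d = 1.18. In 200,000 simulated comparisons the t test gave 85.0%, the uncorrected chi-square test on the median split 71%, and Fisher's exact test 39%.

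The gap between the two tests comes from discreteness. A 10/4 versus 4/10 split has χ² = 28 × (100 − 16)² / 14⁴ = 5.14, so p = 0.023, but Fisher's p is 0.057. Fisher's test needs 11/3 versus 3/11 (p = 0.007).

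**Step 4: type I error if the best of several analyses were reported.** With no treatment effect, 14 per arm, lognormal data with log-SD 0.4 and 200,000 runs:

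- better of raw and log: 5.8%
- best of raw, log and median split, Fisher's test: 5.9%
- best of raw, log and median split, uncorrected chi-square: 8.7%

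A second set-up used change scores with a baseline–post correlation of 0.5 and normal or lognormal data. Its options were raw, log, outlier-clipped, a median split and two tertile cuts, with Fisher's test for the splits. The best of these gave 6.5–7.5% at 14 per arm. At 20 per arm, which is full retention, it gave 10.5–11.6%. Three independent tests would give 1 − 0.95³ = 14.3%; the inflation stays below that because the candidate analyses are correlated.

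None of these runs models the planned mixed model itself.

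**The case against.** **Timing.** A reader might infer that the plan lets the analyst try several scales and report the most favourable one. The text does not support that. It limits transformation to two purposes, and both can be judged on pooled data or residuals without arm labels. Staff processing endpoint data are blinded. That blinding is not tied to the transformation decision, so it does not settle the matter, but choosing after seeing results is only something the text fails to prevent. The type I error figures are therefore conditional.

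**Size of the loss.** A reader might also infer that any transformation costs about a third of the information. It does not. That figure belongs to a median split of a normal outcome, and the article names no split. Finer categories lose less, and a log transform need not lose any. For the skewed data that would prompt the step, the normal-theory figure is only a guide.

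**Scope.** The word used is scores, and the trial also analyses questionnaire scores, for which categories are more natural. But the sentence belongs to the paragraph that sets out the primary contrast, uses the same word as that contrast, and makes no exemption.

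**Detail left to the analysis plan.** Cut-points, triggers and timing are commonly settled there, and their absence from an article is no fault. The point here is different: the article expressly permits categorisation. A later plan could narrow that permission, but as published it reaches the primary outcome.

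**Conclusion.** The point holds as a badly fixed rule about categorisation. As written, the plan permits a continuous primary outcome, powered as a mean change in mg/min/m², to be cut into categories. If that were done, the estimand would change and the result would no longer match the planned contrast or the sample-size basis. The information loss would be 10–36% for five down to two groups of a normal outcome. For a median split at 14 per arm, 85% power would fall to about 39–71%, with the two formula values (63% and 67%) inside that range.

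The effect on type I error is secondary: roughly 6–9% at 14 per arm, under assumed distributions and options, and only if the scale were chosen with arm comparisons in view. Permission for an ordinary transformation such as the log is not in itself a fault.

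**What to change.** In Statistical methods and determination of sample size, remove categorisation as an option for the primary outcome. State that glucose infusion rate will be analysed on one continuous scale, raw or log, fixed before unblinding. Name one sensitivity analysis for outliers or non-normality: either the other scale, or a permutation or bootstrap test of the same contrast. State that it does not replace the primary result.

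The cost is one sentence and one additional sensitivity analysis. No extra participants or measurements are needed.

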**Discussion:**

This trial aims to demonstrate the comparative efficacy and maintenance of different exercise intensities to advance the understanding of PCOS management and provide insight into the optimal exercise intensity for improved cardiometabolic outcomes. Secondary outcomes will include the impact of different exercise protocols on reproductive hormone profiles, mental health and health-related quality of life.

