## Background

Polycystic ovary syndrome (PCOS) is a major public health concern affecting 6–10% of reproductive-aged women worldwide [1]. Insulin resistance is strongly implicated in the aetiology of PCOS and is associated with the reproductive and metabolic consequences of the syndrome [2–7]. Insulin resistance in PCOS is inherent and has been demonstrated to be independent of body mass index (BMI), yet can be exacerbated by obesity [2, 8], although the mechanisms remain unclear. Lifestyle interventions (diet, exercise and/or behavioural) and weight management are the first line therapy [9] for women with PCOS as they improve the clinical symptoms by increasing insulin sensitivity in these women [4, 10].

Moderate intensity aerobic exercise improves metabolic and reproductive features, body composition and psychological well-being in overweight women with PCOS [4, 11, 12]. However, even after exercise interventions a higher level of insulin resistance prevails in women with PCOS compared to women without PCOS, indicating further research is warranted [4]. High intensity interval training (HIIT) is a popular fitness program that encompasses short bouts of high intensity exercise interspersed with active recovery [13]. HIIT has been shown to be acceptable and safe and may assist in addressing barriers reported in women of reproductive age, including time limitations and competing commitments and PCOS-specific barriers such as low confidence and physical limitations [14, 15]. HIIT is enjoyable [4, 16–18] and has been found to have a superior effect on insulin resistance, cardiovascular risk factors and all-cause mortality amongst other predominantly male and older clinical populations [19–22]. Despite this, there is limited comprehensive research on the efficacy of different exercise intensities and optimal exercise intensity for improved cardiometabolic outcomes, reproductive hormone profiles, mental health and health-related quality of life following exercise in PCOS.

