#### Volume matching and training progression

The SSE and HIIT intervention arms will be matched for training volume (metabolic equivalent task (MET).min/week) and progressed weekly by manipulating session duration and intensity. Both SSE and HIIT will progress from 312 MET.min/week in week 1 to 530 MET.min/week in weeks 6–12, meeting exercise guidelines [40]. Exercise sessions will include warm-up and cool down protocols, and will be adjusted weekly to individual capabilities and training adaptations [4, 41]. See Table 1 for details.

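### The stated 85% power rests on a response to training and cannot be read as the power for HIIT versus SSE, a planned contrast between two volume-matched training arms

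*Protocol article*

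**What the plan says.** The only power statement is in the protocol article, under Statistical methods and determination of sample size. It takes a change in insulin sensitivity of "27 mg/min/m^2^ (effect size (Cohens d) = 0.25) in response to training [4", says "we require a total of 42 participants or" 14 per group "to achieve a power of 85" percent at α = 0.05, and recruits 60 to allow for 30% attrition.

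The same section defines the primary analysis: "The HIIT group will be compared with the SSE and Con groups using a planned contrast of change" from baseline to week 12. SSE and Con are named together and neither is ranked first.

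SSE is not an untreated comparator. Table 1 gives it three supervised 50-minute sessions a week. Under Volume matching and training progression, "The SSE and HIIT intervention arms will be matched for training volume", and both arms progress from 312 to 530 MET.min/week. Con receives advice only, and Table 1 expects little added exercise there.

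The Background cites source [4], from which the 27 is taken, among the references for this sentence: "Moderate intensity aerobic exercise improves metabolic and reproductive features, body composition and psychological well-being in overweight women with PCOS [4, 11, 12". The same section also cites [4] for HIIT being enjoyable.

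The Abstract says the trial is meant to "provide insight into the optimal exercise intensity for improved cardiometabolic outcomes". The closing Discussion names the lack of volume-matched comparisons of HIIT with moderate exercise as the evidence gap.

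**The concern.** A response to training is something both exercise arms should show. It can serve as an effect size for a trained arm against an untrained one, or as a before-after change within a trained arm. It is not a difference between two kinds of training. If SSE gained the full 27 mg/min/m², HIIT would have to gain 27 + 27 = 54 for the two arms to differ by 27, and the article offers no basis for that.

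Because there is a single power statement and it sits beside the planned contrast, a reader will apply the 85% to HIIT versus SSE as well as to HIIT versus Con. A non-significant HIIT-SSE result could then be taken as good evidence that intensity makes no difference, although no HIIT-SSE difference was ever specified for sizing. Correcting the effect-size label or supplying an SD would not cure this: the 27 would still be a training response.

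**Working it through.** **Inputs from the article.** Effect 27 mg/min/m²; standardised effect 0.25, labelled Cohen's d; 14 per group, 42 in total; power 85%; α = 0.05 (sidedness not stated, two-sided assumed); three arms at 1:1:1; 30% attrition and 60 recruited. No SD and no expected HIIT-SSE difference are given.

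**1. The plan's own figure.** Attrition reproduces: 42 / 0.70 = 60. The 42 does not follow from the stated inputs.
- Taken as labelled, d = 0.25 implies SD = 27 / 0.25 = 108. For two arms of 14 the noncentrality is 0.25 × √(14/2) = 0.66, and two-sided power is about 10%. Reaching 85% would need about 288 per arm.
- Read instead as Cohen's f = 0.25 for a group-by-time interaction (three groups, two times, correlation 0.5), N = 42 gives 80% and 85% needs N = 48. N = 42 gives about 85% only with an unstated correlation near 0.56.

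This is a separate problem. The next steps set it aside by granting the plan its 85%.

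**2. SD that would make the 85% true at 27.** Pairwise contrast, two-sided 0.05, pooled error df = 42 − 3 = 39. Power = P(|T| > t₀.₉₇₅,₃₉), where T is noncentral t with noncentrality δ = d × √(n/2). Solving for 85% at n = 14 gives δ = 3.07, so d = 3.07 / √7 = 1.16 and SD of change = 27 / 1.16 ≈ 23.2 mg/min/m². This SD is back-solved and is not in the article.

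**3. Power for HIIT versus SSE.** The difference is an assumed fraction of 27. The right-hand column is the full 60 women with no dropout (df = 57).

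| HIIT minus SSE | mg/min/m² | d | Power, 14 per arm | Power, 20 per arm |
|---|---|---|---|---|
| 100% of 27 | 27 | 1.16 | 85% | 95% |
| 75% of 27 | 20.25 | 0.87 | 61% | 77% |
| 50% of 27 | 13.5 | 0.58 | 32% | 44% |
| 25% of 27 | 6.75 | 0.29 | 12% | 15% |

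Using only the two arms' own error df (26 and 38) and re-solving for the SD moves the figures in the last three rows by less than half a percentage point.

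**4. Check under the interaction reading.** With f = 0.25, N = 42 and correlation 0.5 to 0.6:
- If both exercise arms respond equally, all the omnibus power comes from exercise versus Con, and the HIIT-SSE test rejects at its 5% level.
- If SSE lies midway between Con and HIIT, HIIT-SSE power is about 34% to 41%.

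The conclusion does not depend on which reading of 0.25 is used.

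**The case against.** **What the 27 is.** A reader might infer that it is a difference between exercise and no exercise. The article says only that it is a response to training, which may equally be a before-after change within a trained group. Nor is the type of training settled, since source [4] is cited both for moderate exercise and for HIIT. That SSE would gain the full 27, and hence the 54, is therefore plausible but not established. What survives is narrower: on neither reading is the 27 a HIIT-SSE difference, and the article does not claim that it is.

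**Rank of SSE.** A reader might infer that SSE is the main comparator. The statistical section names SSE and Con together, and Outcome measurements refers to all three interventions. The emphasis on intensity comes from the Abstract and Discussion. The point needs only that HIIT versus SSE is one of the planned primary contrasts.

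**Illustrative SD.** The figures rest on an SD the article does not contain. With the SD of 108 implied by d = 0.25, power at 14 per arm is about 10% even for the full 27 and 5% to 8% for the fractions, so the choice of comparator hardly matters. This is correct, and it is why the table is an illustration and not an estimate. The mismatch of contrast would remain once d and n were reconciled.

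**Harm.** No passage plans an equivalence claim, the hypothesis is superiority of HIIT, and the Discussion presents the trial as informing larger ones. Misreading of a null result is a risk, not something the plan states.

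**Condensed article.** The sizing basis is stated, and it does not fit a contrast stated in the same section, so this is not a detail left to a fuller document.

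**Conclusion.** The point holds in limited form. The article's 85% at 14 per group is built on a response to training and cannot be read as the power for HIIT versus SSE, where both arms train at matched volume. No HIIT-SSE difference is stated, and none of 27 mg/min/m² is supported.

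The size of the shortfall is unknown, because it depends on that missing difference. Granting the plan its 85% at 27, power falls to roughly 61% to 12% at 14 per arm, or 77% to 15% at 20 per arm, over assumed differences of 75% down to 25% of 27. These figures assume a two-sided 5% test, a common SD of change of 23.2 and equal arms.

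A reader might also infer that the 85% is sound for exercise versus Con. The article does not support that either: it never calls the 27 a difference from Con, and the labelled d = 0.25 gives about 10% power at 14 per arm.

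**What to change.** In the sizing paragraph:

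1. State what the 27 mg/min/m² is in source [4] (a within-group change or a between-arm difference) and the type of training behind it.
2. Say which contrast the stated power refers to, and do not present the 85% as covering HIIT versus SSE.
3. Give the HIIT-SSE difference detectable at the planned size: about 1.16 SD of change for 85% power at 14 per arm, two-sided 0.05. Convert it to mg/min/m² once an SD of change is given.
4. State that a non-significant HIIT-SSE test will not be read as equal efficacy of the two intensities. Reporting that contrast with its 95% confidence interval would help, but is secondary.
5. Do not assert 85% power for exercise versus Con until d = 0.25 and n = 14 have been reconciled.

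The cost is the rewording of one paragraph and a less favourable stated power for the intensity question. Enrolment, interventions and the planned contrast are unchanged.
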